## Abstract

**Background/Objectives**: Chronic obstructive pulmonary disease (COPD) remains a major global health problem, affecting over 300 million people worldwide. Its high morbidity and mortality rates impose substantial psychosocial and financial burdens on patients and healthcare systems. In the emergency setting, managing acute exacerbations of COPD (AECOPD) poses a major clinical challenge, as these patients often present with multi-organ dysfunction secondary to hypoxia and hypercapnia. Identifying reliable prognostic biomarkers could improve early risk stratification, guide therapeutic decisions, and enhance patient outcomes. **Methods**: This multicenter, prospective, observational study aims to evaluate the prognostic significance of several novel biomarkers—resistin, club cell secretory protein 16 (CC16), interleukin-6 (IL-6), tumor necrosis factor-alpha (TNF-α), S100β protein—alongside conventional markers such as N-terminal-pro–B-type-Natriuretic-Peptide (NT-proBNP), D-dimer, high-sensitivity troponin I (hs-cTnI), C-reactive protein (CRP), and procalcitonin in patients with AECOPD admitted to the Emergency Department (ED). Blood samples will be collected at admission. The novel biomarkers (resistin, CC16, IL-6, TNF-α, S100β) will be measured using standardized ELISA kits, while conventional biomarkers (NT-proBNP, troponin I, CRP, procalcitonin) will be analyzed using routine automated clinical laboratory methods. Correlations between biomarker levels, clinical and imaging data, severity scores (GCS, SOFA, CFS, Ottawa COPD Risk Scale, DECAF, BAP-65), and short-term outcomes (hospital discharge status and 28-day survival) will be assessed. The study has received approval from the Ethics Committee of the “Iuliu-Hatieganu” University of Medicine and Pharmacy, Cluj-Napoca, and all participating hospitals. Written informed consent will be obtained from all participants or their legal representatives. **Results:** This study protocol does not report results, as data collection and analysis are ongoing. **Conclusions /Expected Impact:** By identifying novel biomarkers with prognostic and pathophysiological relevance, this research aims to inform the development of early risk stratification tools and support future evidence-based approaches to the management of critically ill COPD patients in the ED.

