### 2.3. Sample Size and Study Duration

The study is planned to include approximately 100 consecutive eligible patients admitted over a 15-month period. The sample size was estimated based on local patient volumes and previous annual ED statistics (over 600 COPD admissions per year), ensuring sufficient statistical power to detect correlations between biomarker levels and clinical outcomes. Baseline biomarker values will be analyzed exclusively for prognostic correlation with the later need for oxygen therapy, NIV or IMV, and will not be used to guide acute therapeutic escalation or de-escalation.

Based on an estimated annual number of approximately 600 COPD presentations to the ED, we anticipated enrolling around 100 eligible patients meeting the study inclusion criteria. In these participants, five biomarkers (resistin, CC16, IL-6, TNF-α, and S100β protein) will be measured and correlated with disease severity and short-term outcomes.

A post hoc power analysis performed using G*Power software (version 3.1.9.7) for a two-tailed Mann–Whitney test, assuming a large effect size (Cohen’s d = 0.8) and a Bonferroni-adjusted significance level (α = 0.01), indicated a statistical power (1 − β) of approximately 0.91–0.92. This suggests that a sample size of 100 participants could be adequate for detecting large and clinically relevant differences in biomarker levels between well-defined severity or outcome groups. In patients with acute exacerbations of COPD, Vassiliou et al. reported higher serum resistin levels during the acute phase as compared to the stable phase after clinical recovery (median at admission 19.44 ng/mL vs. 9.70 ng/mL at follow-up), indicating a large difference between clinically distinct states [4]. We will reevaluate the sample size after enrollment of 20 patients, and we plan to extend the study to other centers, if necessary.

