### 2.4. Ethical Considerations

The study has received ethical approval from the Ethics Committee of “Iuliu-Hatieganu” University of Medicine and Pharmacy Cluj-Napoca (No. AVZ 71/20 March 2025) and from the Ethics Committee of Cluj-Napoca County Emergency Clinical Hospital (No. 9333/17 March 2025). The study will comply with the Declaration of Helsinki, the European Union General Data Protection Regulation, and national research ethics legislation. All participants (or their legal representatives) will provide written informed consent prior to enrollment.

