#### 2.5.4. Data Monitoring

At ED admission, all patients will undergo assessment using validated severity and prognostic scores available on the MDCalc platform (www.mdcalc.com). The following tools will be applied: mMRC Dyspnea Scale for grading dyspnea severity, the SOFA score, GCS, for evaluating neurological impairment secondary to hypoxia or hypercapnia, and the CFS, adapted for triage levels used in Romania, to estimate frailty and predict mortality. Additional prognostic scores specific to COPD will be applied, including the Ottawa COPD Risk Scale (predicting 30-day mortality or severe adverse events such as myocardial infarction or the need for intubation), the DECAF Score for in-hospital mortality in acute exacerbations of COPD, and the BAP-65 Score for in-hospital mortality prediction.

Serum biomarker levels will be measured according to the previously described analytical protocol. Based on clinical status and therapeutic requirements, study participants will be classified into three groups: COPD patients requiring supplemental oxygen therapy, those requiring NIV, and those requiring IMV. These measurements are intended solely to establish prognostic associations with subsequent respiratory support requirements and will not influence real-time clinical management.

At discharge from the ED or before hospitalization in the Pulmonology Department or the Internal Medicine Department, patient outcomes will be documented as improved (reduction in dyspnea and clinical instability, no requirement for escalation of respiratory support, decreased level of respiratory support, and evidence of improving gas exchange), stable (no significant improvement but no deterioration, with the same level of respiratory support maintained), worsened (increased respiratory distress, need for escalation of respiratory support, and worsening gas exchange or hemodynamics), or deceased (ED mortality). The total duration of hospitalization will be recorded, as well as survival time, including the date of death if it occurred during the ED stay or hospitalization. Early survival will additionally be assessed at 28 days through telephone follow-up.

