## Figures and Tables

**Table 1 diagnostics-16-00122-t001:** Objectives proposed by the research team.

Primary Objective	Secondary Objectives
To evaluate the association between serum levels of resistin, CC16, IL-6, TNF-α, and S100β measured at ED admission and early outcomes, including discharge status and 28-day survival, in patients presenting with acute exacerbations of COPD (AECOPD).	To determine biomarker cutoff values associated with the need for escalation of respiratory support (oxygen therapy, non-invasive ventilation, or invasive mechanical ventilation).
	To identify combinations of circulating biomarkers and established clinical scores that best predict short-term mortality and organ dysfunction.
	To assess the relationship between diaphragmatic contractility evaluated by bedside ultrasound and circulating biomarker levels, in relation to the level and duration of ventilatory support.
	To explore the potential role of biomarker-based risk stratification in informing clinical decision-making for AECOPD patients in the ED.

Legend: CC16—club cell secretory protein 16; IL-6—interleukin-6; TNF-α—tumor necrosis factor-alpha; S100β—S100 calcium-binding protein beta; ED—Emergency Department; COPD—chronic obstructive pulmonary disease; AECOPD—acute exacerbation of chronic obstructive pulmonary disease.

**Table 2 diagnostics-16-00122-t002:** Inclusion criteria for eligible study participants.

Inclusion Criteria	
Age ≥ 50 years. Confirmed prior diagnosis of COPD, regardless of disease stage or ongoing therapy:	
(a) the GOLD spirometric grades	GOLD I (FEV_1_ ≥ 80%) GOLD II (50% ≤ FEV_1_ < 80%) GOLD III (30% ≤ FEV_1_ < 50%) GOLD IV (FEV_1_ < 30%)
(b) ABE category assessment	A—low symptom burden and low risk of exacerbations; 0–1 moderate exacerbations in the previous year, with no hospitalizations B—increased symptoms but low risk of exacerbations; 0–1 moderate exacerbations in the previous year, without hospitalization E—high exacerbation risk, defined as ≥ 2 moderate exacerbations or ≥1 exacerbation requiring hospitalization in the previous year, irrespective of the level of symptoms
Admission to the ED with acute exacerbation of COPD. Signed informed consent obtained from the patient or legal representative.	

Legend: COPD—chronic obstructive pulmonary disease; GOLD—Global Initiative for Chronic Obstructive Lung Disease; FEV_1_—forced expiratory volume in 1 s; ED—Emergency Department.

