**Table 3 diagnostics-16-00122-t003:** Exclusion criteria for eligible study participants.

Exclusion Criteria	
Age < 50 years. Coexisting acute or chronic conditions that could influence respiratory failure:	
(a) respiratory infections without underlying COPD	pneumonia, acute bronchitis, acute pulmonary viral infections (influenza, RSV, SARS-CoV-2, etc.)
(b) respiratory non-COPD causes	pneumothorax, asthma, bronchiectasis exacerbation in the absence of COPD), cystic fibrosis, upper airway obstruction (tumor, foreign body, laryngeal edema), hyperventilation syndrome or panic attack
(c) acute exacerbation of pre-existing interstitial lung disease (ILD)	idiopathic pulmonary fibrosis, interstitial pneumonias associated with connective tissue diseases, sarcoidosis, hypersensitivity pneumonitis, drug- or radiation-associated ILD
(d) cardiac causes	acute heart failure, acute coronary syndromes, cardiac tamponade, clinically significant arrhythmias, cardiogenic shock
(e) thromboembolic disease	pulmonary embolism
(f) metabolic or systemic causes	metabolic acidosis (DKA, renal failure), severe anemia, sepsis from non-pulmonary sources, hypovolemic shock, anaphylactic shock
(g) trauma	burns or trauma of any localization
(h) neurological conditions affecting respiratory function	acute stroke, neuromuscular diseases causing respiratory depression (myasthenia gravis, Guillain-Barré syndrome, amyotrophic lateral sclerosis)
Pregnancy. Cardiac arrest prior to or during ED admission. Terminal—stage neoplastic disease. Patients under custodial measures or unable to provide consent. Failure to obtain informed consent.	

Legend: COPD—chronic obstructive pulmonary disease; RSV—respiratory syncytial virus; SARS-CoV-2—severe acute respiratory syndrome coronavirus 2; ILD—interstitial lung disease; DKA—diabetic ketoacidosis; ED—Emergency Department.

**Table 4 diagnostics-16-00122-t004:** Analytical Performance and Reference Values of the Selected Biomarkers.

Biomarker	ELISA Kit (Elabscience®, Biotechnology Inc., Wuhan, Hubei, China)	Detection Range (Units)	LOD/Sensitivity (Units)	CV% (Intra/Inter)	Specificity/Cross-Reactivity	Normal Values (Adults)
Resistin	Human Resistin ELISA Kit (E-EL-H1213)	0.31–20 ng/mL	<0.19 ng/mL	<10%/<12%	High analytical specificity; no detectable cross-reactivity with other adipokines	3–12 ng/mL; higher in smokers and older adults

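### Table 3 excludes patients who cannot consent, while Table 2, section 2.4 and the abstract admit them through a legal representative, so patients without capacity are both eligible and excluded

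*Protocol article*

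**What the plan says.** Three places in the protocol article allow a representative to consent:

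- Table 2 (inclusion criteria): "Signed informed consent obtained from the patient or legal representative".
- Section 2.4: "All participants (or their legal representatives) will provide written informed consent prior to enrollment".
- Abstract: "Written informed consent will be obtained from all participants or their legal representatives".

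Table 3 (exclusion criteria) lists "Patients under custodial measures or unable to provide consent" and, as a separate item, "Failure to obtain informed consent".

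Section 2.5.4 describes the population to be studied. Participants are sorted into "COPD patients requiring supplemental oxygen therapy, those requiring NIV, and those requiring IMV", and the GCS is applied "for evaluating neurological impairment secondary to hypoxia or hypercapnia". Section 2.3 plans to enrol "approximately 100 consecutive eligible patients admitted over a 15-month period".

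**The concern.** In adults aged 50 or over, a representative's signature is normally needed only when the patient cannot sign. Table 3 removes those same patients, so it largely cancels the provision made in the other three places.

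The patients affected are not a random subset. Capacity at ED admission is plausibly linked to much of what the study measures:

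- **Severity scores.** A low GCS is a direct marker of impaired consciousness, and it is to be recorded.
- **S100β.** The introduction and section 3 justify this marker by cerebral hypoxia and neuronal injury in severe exacerbations. Patients with impaired consciousness are those in whom that signal would be expected.
- **Outcomes.** The primary objective concerns discharge status and 28-day survival. A secondary objective seeks cutoffs for escalation of support up to IMV. Losing the sickest patients would probably reduce deaths and IMV cases. Section 2.5.6 ties the number of model predictors to the number of events (about 5–10 per predictor), so lost events also limit the regression models.
- **Consistency between sites.** Section 2.1 names five hospitals. If some follow Table 2 and others Table 3, the term consecutive eligible patients has no single meaning, and case mix may differ by site for reasons unrelated to disease.

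**Working it through.** **1. The rules applied to three kinds of patient**

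| Patient at ED admission | Table 2, section 2.4, abstract | Table 3, inability to consent | Table 3, consent not obtained |
|---|---|---|---|
| Has capacity and signs | eligible | not excluded | not excluded |
| Lacks capacity, representative signs | eligible | excluded | not excluded |
| Lacks capacity, nobody signs | not eligible | excluded | excluded |

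The conflict is confined to the second row. No other text in the article resolves it.

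**2. Can the Table 3 item be read harmlessly?** It could be taken to mean that neither the patient nor a representative is able to consent. Two features count against this. The item's grammatical subject is the patient. And the third row is already covered by the separate item on consent not obtained, so under the harmless reading the inability item would add nothing.

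**3. Who is affected?** Only patients without capacity at the time of enrolment. Section 1 speaks of the support needed subsequently during hospitalization, and section 2.3 of later need. A patient who consents in the ED and is intubated afterwards is eligible under either rule.

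**4. Illustration of size.** The contradiction rests on no number. The article gives neither the proportion needing IMV nor the proportion lacking capacity, so the smaller group's size below is an assumption.

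Inputs from section 2.3: total 100, d = 0.8, two-sided alpha 0.01, Mann–Whitney test. Method: noncentral t, with each group size multiplied by the Mann–Whitney efficiency factor 3/π (normal data).

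- Noncentrality = d × √(m₁m₂/(m₁+m₂)), with mᵢ = nᵢ × 3/π and df = m₁ + m₂ − 2 = 93.5.
- Critical value: 2.629 at alpha 0.01; 1.986 at alpha 0.05.

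The plan's own figure first. Section 2.3 states power of about 0.91–0.92 without giving the split. At an assumed 50 v 50, the result is 0.912 without the efficiency factor (normal approximation 0.923), and 0.897 with it (normal approximation 0.909). The stated figure is therefore reproduced to within about two points.

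Unequal splits, total held at 100, factor included:

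| Smaller v larger group | Noncentrality | Power, alpha 0.01 | Power, alpha 0.05 |
|---|---|---|---|
| 20 v 80 | 3.127 | 0.69 | 0.87 |
| 15 v 85 | 2.791 | 0.57 | 0.79 |
| 10 v 90 | 2.345 | 0.39 | 0.64 |
| 5 v 95 | 1.704 | 0.18 | 0.39 |

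Example: if 10 of 100 patients would need IMV and half of them were excluded and replaced by patients not needing IMV, the split would go from 10 v 90 to 5 v 95. Power would fall from 0.39 to 0.18 at alpha 0.01, or from 0.64 to 0.39 at alpha 0.05.

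**The case against.** The best defence is that three places agree on representative consent, so the intent can be inferred and Table 3 is one loosely worded clause. That is fair as to intent. It does not settle practice, because staff screening against a printed list of exclusions would act on the list.

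The objections to the size are sound. The power figures depend on assumed rates of IMV and incapacity. They also concern a comparison of IMV with all others at alpha 0.01, which the article does not specify as an analysis. Section 2.5.6 plans correlations, regression, ROC curves and Kaplan–Meier curves, with p < 0.05 throughout. In the example, power is only 0.39 before anyone is excluded, so much of the weakness comes from the assumed imbalance and not from the consent rule.

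Two stronger readings are tempting, and the article supports neither. A reader might infer that Table 3 empties the IMV group. It does not, because patients who consent on arrival and are intubated later remain. A reader might also infer that the ethics committees approved representative consent, so that Table 3 is simply the error. Section 2.4 reports the approvals and, separately, who will consent, but it does not say which consent route was approved.

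Finally, that the excluded patients would be those with low GCS or already intubated is an inference from section 2.5.4, not the article's wording. That sites would diverge is a possibility, not something shown.

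**Conclusion.** The contradiction stands on the text alone. Applied literally, Table 3 would select on capacity at enrolment. The likely direction is a truncated range of severity and S100β, with fewer IMV cases and deaths. This assumes only that incapacity is commoner among the sickest patients, which the study's use of GCS for hypoxic or hypercapnic impairment supports.

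The extent of the loss cannot be determined from the article. The IMV group would shrink by an unknown amount, and the power figures are illustrative only. The matter should be settled now: the abstract says data collection is ongoing, and patients missed at admission cannot be recovered for a baseline blood sample.

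**What to change.** Reconcile Table 3 with Table 2 and section 2.4 so that one consent rule applies at all five hospitals, and check that rule against the ethics approvals. The choice belongs to the sponsor and the ethics committees.

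- **If representative consent stands**, as three places state, delete the inability clause from Table 3 or limit it to patients with no representative. Deletion is cleaner, because the separate item on consent not obtained already covers that case.
- **If it does not stand**, remove the representative wording from Table 2, section 2.4 and the abstract, and restrict the conclusions, including those on S100β and IMV cutoffs, to patients with capacity at ED admission.

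In either case, keep a screening log of the number excluded for lack of capacity, by respiratory-support level, so that any selection can be reported. Establish from sites already enrolling which rule they have used.

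The cost is a short amendment and one extra field in the screening log. If the chosen rule differs from what was approved, ethics review of the change is also needed.

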## Data Availability

No new data were created or analyzed in this study. Data sharing is not applicable to this article.

## Abbreviations

The following abbreviations are used in this manuscript:

AECOPD	Acute Exacerbation of Chronic Obstructive Pulmonary Disease
ALT	Alanine Aminotransferase
AST	Aspartate Aminotransferase
BAP-65	Blood urea nitrogen, Altered mental status, Pulse ≥ 109/min, Age ≥ 65 years score
CC16	Club Cell Secretory Protein 16
CFS	Clinical Frailty Scale
CO_2_	Carbon Dioxide
COPD	Chronic Obstructive Pulmonary Disease
CRP	C-Reactive Protein
CT	Computed Tomography
CV	Coefficient of Variation
DBP	Diastolic Blood Pressure
DECAF	Dyspnea, Eosinopenia, Consolidation, Acidemia, Atrial Fibrillation score
DKA	Diabetic Ketoacidosis
ED	Emergency Department
ELISA	Enzyme-Linked Immunosorbent Assay
EtCO_2_	End-Tidal Carbon Dioxide
EU	European Union
FEV_1_	Forced Expiratory Volume in 1 Second
FiO_2_	Fraction of Inspired Oxygen
GCS	Glasgow Coma Scale
GDPR	General Data Protection Regulation
GOLD	Global Initiative for Chronic Obstructive Lung Disease
HCO_3_^−^	Bicarbonate
hs-cTnI	High-Sensitivity Cardiac Troponin I
IFN-γ	Interferon Gamma
IL-6	Interleukin-6
ILD	Interstitial Lung Disease
IMV	Invasive Mechanical Ventilation
IQR	Interquartile Range
LOD	Limit of Detection
MAP	Mean Arterial Pressure
mMRC	Modified Medical Research Council Dyspnea Scale
NIV	Non-Invasive Ventilation
NT-proBNP	N-terminal pro–B-type Natriuretic Peptide
PaCO_2_	Partial Pressure of Arterial Carbon Dioxide
PaO_2_	Partial Pressure of Arterial Oxygen
pH	Potential of Hydrogen
ROC	Receiver Operating Characteristic
RSV	Respiratory Syncytial Virus
SBP	Systolic Blood Pressure
SARS-CoV-2	Severe Acute Respiratory Syndrome Coronavirus 2
SCGB	Secretoglobin Protein Family
SD	Standard Deviation
S100β	S100 Calcium-Binding Protein Beta
SOFA	Sequential (Sepsis-Related) Organ Failure Assessment
SpO_2_	Peripheral Oxygen Saturation
T°C	Core Body Temperature (degrees Celsius)
TNF-α	Tumor Necrosis Factor Alpha
